## **Neurofeedback Day (mbNF or control NF)**

### ***Mental Noting training***

After the baseline resting state scan, subjects will learn a “mental noting” mindfulness practice to use during the neurofeedback scans. Trained research staff will provide this semi-structured 45-minute training established in our prior work. Mental noting is a major component of Vipassana (insight mindfulness meditation); key principles include “concentration”, “observing sensory experience”, “not ‘efforting’”, and “contentment”. Subjects will be taught to mentally label/note whatever sensation is most prominent in their sensory experience from moment to moment (e.g., seeing, hearing, feeling, thinking). This practice primarily trains the “attention and control” mindfulness components, but also influences “attitude” by recognizing that “one’s thoughts and feelings are temporary, objective events in the mind, as opposed to reflections of the self that are necessarily true”, sometimes referred to as “decentering”. Training also will include identifying personal scenarios in which mental noting could be applied, explaining the goal of using these strategies to manage distress in daily experiences. Before the MRI scan, subjects will practice mental noting practice by verbalizing their mental label out loud to the study staff, who will observe the practice and provide feedback as needed. Subjects will then complete a silent practice of mental noting while viewing a simulation of neurofeedback. All subjects will be trained until they feel competent to use mental noting in the scanner. During mbNF (6 runs, 2.5 mins each), subjects will use mental noting with the aim of controlling the visual feedback; specifically, they will try to move the position of the white dot toward the (upper) red circle and away from the (lower) blue circle (**Fig 1**).

### ***Mental Noting task with Neurofeedback***

During NF, subjects will receive feedback indicating differential activation between DMN and FPCN. As in our previous studies we will use the multivariate and univariate real-time functional imaging (MURFI) package to deliver continuous neurofeedback. Prior to the pre-mbNF resting state run, a brief (2 frame) fMRI localizer will be acquired. During acquisition of the pre-mbNF resting state, we will register personalized network maps from T1 standard MNI space to fMRI space via a linear transform, and trained staff will manually inspect the quality of alignment. We will implement our established neurofeedback protocol, where continuous visual feedback signifies the level of FPCN-DMN activation difference. We will adapt a real-time fMRI computational pipeline described in detail in our previous work. An incremental general linear model (GLM) will be used to compute moment-to-moment variation in activation voxelwise, while accounting for nuisance sources

(e.g. low-frequency signal drifts) computed online. At each timepoint, the GLM will estimate residual signal (based on measured minus expected voxel intensity) that has two components: BOLD signal fluctuations and unmodeled noise. The residual will be scaled by an estimate of voxel reliability (the average GLM residual over the first 15 frames, considered as baseline). Activation within the FPCN and DMN will each be estimated separately, based on the median of all voxels within each network. A trigger signal will be sent to a stimulus presentation computer to control visual feedback. The visual feedback, based on a subtraction of FPCN minus DMN activation, will consist of a rectangle with one centrally displayed white dot and two circles, including a red hollow circle located above and a blue hollow circle located below the white central dot (**Fig 1**). As the FPCN minus DMN difference increases positively (i.e., in the direction of FPCN activation coupled to DMN deactivation), the central white dot will move upward (toward the red circle). As the FPCN minus DMN difference increases negatively, the central white dot will move downward (toward the blue circle). Subjects will aim to volitionally move the central white dot continuously and consistently toward the red using mindfulness strategies.

### **Psychotherapy (DBTsg)**

DBTsg will be a weekly 2-hour group that subjects join by secure videoconference (e.g. Zoom) through the UMass Psychological Services Center. DBTsg will follow the 20-week McMain protocol which led to improvement in treatment > control patients on emotion regulation, distress tolerance, anger, and suicidal/self-harming behaviors. Each subject cohort will proceed through the McMain-protocol DBT modules: Distress Tolerance (4 sessions including skills for “crisis survival,” “distracting,” and “radical acceptance”), Dialectics (4 sessions, including skills for validation, “walking the middle path,” and increasing positive behaviors), Emotion Regulation (4 sessions, including skills for observing and describing emotions, reducing vulnerability to negative emotions, and “opposite action”), and Interpersonal Effectiveness (4 sessions, including skills for clarifying priorities in interpersonal situations, relationship effectiveness, and maintaining self-respect). Each module is preceded by one week focused on mindfulness. We selected this protocol because it is the longest of the evidence-based skills group protocols, with 5 full months of treatment (approaching the 6-month classical schedule).

The DBT groups for this study will be directed by [name], who is a clinical psychologist licensed in CT and MA, certified DBT trainer who routinely supervises doctoral students in DBT. We expect this treatment dose to provide meaningful benefit to patients while also facilitating our study design. Admission to the DBTsg program will be rolling, with new subjects admitted on the mindfulness day at the beginning of each module. DBTsg will run continuously throughout the year so subjects can join at the beginning of any module and graduate once they have participated in four full modules. In this way, we can stagger subjects to facilitate the scheduling of NF scans and complete a full cohort.

All DBTsg zoom sessions will be recorded, and participants must agree to video recording in order to be included in the study.

Before, during, and after psychotherapy, mental healthcare use and needs will be tested as exploratory outcomes:

a) (for during study psychotherapy) DBTsg group attendance (scored by study staff by watching videos)

b) use of scheduled and unscheduled mental healthcare resources outside the study (question included in surveys at each assessment timepoint)

### ***Program Evaluation of Subject Experience***

We will use a phased approach to evaluate acceptability of the intervention. We will measure subject experience in the domains of tolerability and satisfaction for each of the study procedures in order to ensure that we develop an intervention that will, if effective, be adopted by the target population.

To assess tolerability, we will consider intervention schedule and physical/emotional adverse events.

For satisfaction assessment, subjects will rate treatment expectations, motivation, and likelihood of future participation. Surveys (e.g. Intrinsic Motivation Inventory (IMI)) will quantify participant experience performing NF. Qualitative approaches will query what subjects enjoyed most, what challenges they faced, and their recommendations for improvement.

There will be three phases of the evaluation: setup and planning, pilot, and implementation.

***1. Setup and planning*** The first six months of the R61 will be focused on project setup and procedure piloting, including mbNF protocol setup at Yale and initial work on the program evaluation plan. [name] and [name] will travel to Yale to for pilot tests. [name] will experience the full protocol and will observe several test subjects in order to define the program evaluation plan.

***2. Pilot phase (1.5 years)*** Data from the first six months will inform the evaluation plan for the first 52 subjects (the NIH R61 phase of the grant). This phase will include testing of self-report questions and exploratory qualitative components, such as post-NF interviews and intermittent focus groups, allowing us to determine the best approaches to measure acceptance and tolerability of the intervention.

***3. Implementation of program evaluation (3 years)*** The final program evaluation plan will be implemented with the subsequent 72 subjects (R33 phase of the NIH grant). Self-report questions for program evaluation will be added to the surveys at baseline, pre-NF, post-NF, and follow-up timepoints. Research assistants will be trained to collect responses to program evaluation questions during the post-NF debriefing. [name] may also conduct intermittent focus groups by videoconference with subsets of subjects to further explore areas of particular interest. If between-group differences are identified in measures of subject experience, they may be explored as potential moderators of intervention effects. Data from program evaluation will be critical to design of subsequent studies to further develop this intervention and included in manuscripts describing this project.

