**Randomization and control condition**

Subjects assigned to receive NF at each site (Yale and MGH) will be randomized within-site using a predetermined randomization schedule prepared and known only to the site neuroimaging staff (the rest of the study staff will remain blinded). Each schedule will result in 1:1 randomization with the constraint that the number of mbNF cases is always  $\geq$  the number of control-NF cases (necessary to ensure each control subject has a prior mbNF subject to be matched to) and also the constraint that the number of mbNF cases does not exceed the number of control-NF cases by more than three (to keep the two groups reasonably balanced over time). Clinical staff and assessment raters will remain blind to group assignment. Subjects will be debriefed at the end of the study and at that time their group assignment will be disclosed.

**Yoked-sham feedback** Subjects in the control-NF group will complete the mindfulness training and undergo similar MRI scan procedures. The primary difference in scans is that the control-NF subjects will not receive feedback based on their own brain's activity but will receive feedback based on data extracted from a previously-acquired mbNF session with a different study subject. Thus, the visual display will be independent from the subject's own brain activity in the control-NF group. This ensures that subjects across groups are viewing equivalent stimuli. This yoked sham control approach was chosen for this study because it allows for subject blinding, creates a similarly engaging feedback training experience, and balances positive feedback received across groups. Specifically, a control-NF subject receives feedback indicating they are having the same amount of success as the NF subject they are yoked to. The perception of success can impact motivation because it is easier to stay motivated if the participant feels they are having some success. It is also likely to affect

the magnitude of the placebo effect, because if a participant sees that they are successful in controlling their mindfulness-related brain patterns, they are likely to have a larger placebo effect. Thus, controlling for perception of success is critical.

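### An arm difference in participant experience is made the trigger for an exploratory moderator analysis, although after neurofeedback such a difference reflects the arm or an imperfect sham

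*Protocol*

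**What the plan says.** The rule stands under Implementation of program evaluation in section 5.1: "If between-group differences are identified in measures of subject experience, they may be explored as potential moderators of intervention effects". An observed arm difference is what makes a measure a candidate.

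The measures are mixed in content and timing. "For satisfaction assessment, subjects will rate treatment expectations, motivation, and likelihood of future participation", and surveys such as the Intrinsic Motivation Inventory (IMI) "will quantify participant experience performing NF". On timing: "Self-report questions for program evaluation will be added to the surveys at baseline, pre-NF, post-NF, and follow-up timepoints". So some ratings precede NF and some follow it, and a rating of what it was like to perform NF can only follow it. The rule does not separate the two kinds.

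The same section, under Randomization and control condition, explains the choice of a yoked sham. It "creates a similarly engaging feedback training experience, and balances positive feedback received across groups". The reasoning continues: "The perception of success can impact motivation because it is easier to stay motivated if the participant feels they are having some success". Perceived success is also said to be likely to affect the size of the placebo effect, and the paragraph ends: "Thus, controlling for perception of success is critical". The next paragraph concedes that control participants might notice that the display does not follow their own state. It therefore plans to ask, at the closing debriefing, which arm participants believe they were in and how confident they are. It gives no consequence for an arm difference in experience.

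**The concern.** A moderator should be a characteristic that allocation cannot have changed, chosen because it might alter the treatment effect. Choosing it because the arms differ fails either way. If the rating precedes NF, the difference is a chance imbalance and says nothing about effect modification. If the rating follows NF, the rule favours the very measures that allocation has altered.

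In the second case, comparing arms at the same level of experience is no longer a randomised comparison. People who report high engagement on genuine feedback and people who report it on a replayed recording need not have the same prognosis. The display in the control arm is unrelated to the viewer's own brain activity, so the link between felt success and prognosis could plausibly differ by arm without any treatment effect. An interaction test would read that as moderation.

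The rule also sits badly with the protocol's own argument for the sham. If matched perceived success is critical because it drives motivation and placebo response, a post-NF arm difference in motivation bears first on whether the sham worked and whether a rival explanation exists for any BSL23 difference. The rule sends that evidence to effect modification instead. At stake are exploratory statements, for example that mbNF helps those who felt engaged. The protocol says the evaluation data will appear in the manuscripts and will be critical to the design of later studies.

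**Working it through.** The protocol gives no figure for this analysis, so there is none to reproduce. The check is a simulation with stated assumptions.

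**Inputs from the protocol**
- 1:1 allocation (section 5.1).
- 72 participants under the final evaluation plan (section 5.1), so 72/2 = 36 per arm.
- 62 per arm for the full clinical sample (section 5.4.1). This larger number may apply to the IMI, which is listed in Table 1 for all enrolled participants.

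**Assumptions (not in the protocol)**
- No mbNF effect on the outcome.
- A post-NF experience score M that differs between arms by d = 0.5 SD.
- A within-arm correlation between M and outcome change of r1 in mbNF and r0 in control.
- Two-sided 5% tests, 8,000 simulated trials per setting.

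**Model.** Let A = 1 for mbNF and 0 for control, with Z and e independent standard normal:
- M = d·A + Z
- Y = r·Z + √(1 − r²)·e, where r = r1 or r0 according to arm.

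The marginal mean of Y is the same in both arms, so the unadjusted arm test holds 5%. Given M, the expected outcome is r1·(M − d) in mbNF and r0·M in control. Two consequences follow:
- The apparent interaction slope is r1 − r0, although mbNF does nothing.
- If r1 = r0 = r, the slope difference is zero, but the arm effect at a common M is −r·d. For r = 0.3 this is 0.3 × 0.5 = 0.15 SD; for r = 0.4 it is 0.4 × 0.5 = 0.20 SD.

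**Hand check of one cell** (r1 = 0.3, r0 = 0, 36 per arm). The standard error of the slope difference is about √((0.91 + 1)/36) = 0.230. The ratio is 0.3/0.230 = 1.30, and the rejection rate is about Φ(1.30 − 1.96) ≈ 0.26. The simulation gives 0.24.

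**Simulated rate of a falsely significant arm-by-experience interaction**

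| r1 (mbNF) | r0 (control) | 36 per arm | 62 per arm |
|---|---|---|---|
| 0 | 0 | 5% | 5% |
| 0.2 | 0 | 13% | 20% |
| 0.3 | 0 | 24% | 38% |
| 0.4 | 0 | 39% | 62% |
| 0.3 | 0.15 | 9% | 14% |
| 0.4 | 0.2 | 14% | 22% |
| 0.3 | 0.3 | 5% | 5% |
| 0.4 | 0.4 | 5% | 5% |

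Repeat runs move these rates by about one percentage point.

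**Effect of the selection step.** A true d = 0.5 in experience is flagged at p < 0.05 in about 55% of trials at 36 per arm and 79% at 62. In the rows with r0 = 0, the chance of being both flagged and falsely significant is about 7%, 13% and 21% at 36 per arm, and 15%, 30% and 49% at 62.

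**Second model.** Here M and the outcome share an unmeasured prognostic factor, which explains half the variance of M and correlates 0.5 with the outcome. The implied correlation of M with outcome is √0.5 × 0.5 = 0.354. The predicted bias in the arm effect given M is 0.354 × 0.5 = 0.18 SD for a 0.5 SD shift and 0.354 × 0.8 = 0.28 SD for a 0.8 SD shift. The simulation gave the same values, with the interaction test near 5%. When, with a 0.8 SD shift, the arm also removed almost all of the link between M and prognosis, false interactions rose to 22% (72 participants) and 35% (124).

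**After the fix.** With an M that the arm cannot shift, as for a pre-NF rating, the second model gives 5.0% and 5.5% for the interaction test and 5.1% and 5.2% for the arm effect given M (72 and 124 participants), with no bias.

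**The case against.** The strongest reply is that this is an optional exploration inside an acceptability programme. It feeds no objective, no listed outcome and no numbered analysis in section 5.4.1, and the evaluation plan is to be finalised after the pilot phase. All of that is true and limits the weight of the point. It does not rescue the rule: the protocol states the selection criterion, and calling the analysis exploratory does not make an arm difference a valid reason to choose a moderator.

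Several stronger readings are tempting, and the protocol does not support them:
- *That the plan commits to these moderator analyses.* The wording is permissive: such measures may be explored.
- *That every experience measure is a consequence of the arm.* Ratings are taken at "baseline, pre-NF, post-NF, and follow-up timepoints". A difference in the first two is chance.
- *That a failed sham would go unnoticed.* The rule operates only once the arms have been compared on experience, so an imbalance would be seen. The debriefing also asks for believed assignment. What is missing is an instruction to read an experience difference as evidence on the sham.
- *That false moderation is automatic.* It needs an experience–outcome relation that differs by arm (or, as a variant run showed, is curved). The highest rates require zero correlation in control. That is an extreme case: yoking detaches the display from the person, not the person's interest or effort.
- *That the BSL23 or connectivity results are compromised.* Their planned tests do not use these measures.

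It is also fair that nothing in the protocol supports d = 0.5, since the yoking is meant to make the difference small.

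**Conclusion.** The point holds as a criticism of an exploratory rule. An arm difference is not a sound basis for choosing a moderator. For post-NF measures it selects variables affected by allocation and passes over the reading that the protocol's own case for the sham requires.

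The size depends on assumptions. With no mbNF effect and d = 0.5, false interactions range from the nominal 5% (equal or zero correlations) through 9–14% (control at half the mbNF correlation of 0.3 or 0.4) to 13–39% (no correlation in control, 0.2 to 0.4 in mbNF) at 36 per arm. The corresponding ranges at 62 per arm are 14–22% and 20–62%. Where the correlations are equal, the error moves to the arm effect read at a given experience level, at 0.15 to 0.20 SD for correlations of 0.3 to 0.4. The direction of that bias depends on which arm reports the better experience. If experience is unrelated to outcome, there is no inflation.

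**What to change.** Replace the sentence in section 5.1 with wording such as:

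> Exploratory moderator analyses will use only expectation and motivation ratings collected at baseline or before the NF runs, chosen regardless of arm differences. Post-NF and follow-up experience measures (including the IMI) will be compared between arms and reported, with the believed-assignment data, as evidence on sham equivalence. Any difference will be discussed as a possible mediator or rival explanation of the primary result, not as a moderator.

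This needs no new data: program-evaluation questions are already planned before NF, and the post-NF ratings and debriefing answers are already to be collected. The cost is one sentence, and post-NF ratings can no longer support subgroup claims.

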#### **5.1.1 Data Collection**

All documentation of consent, surveys, and interview assessment for this project will be stored in a Yale-based instance of REDCap. Separate REDCap projects will be used for consent with participant identifiers and main data collection (without identifiers, using an alphanumeric code for each participant to provide a link to the consent project and the MR data).

Clinic notes at U Mass will be maintained in the clinic's electronic medical record, including a copy of the clinical intake summary and safety plan (generated by REDCap reports).

MRI data will be stored without participant identifiers on secure servers.

De-identified data will also be transferred to the National Data Archive at regular intervals in order to comply with the mandates of the National Institutes of Health.

### **5.1.2 Adverse Events Definition and Reporting**

No significant adverse events are expected for this intervention. We will query subjects at every clinical assessment for such events. If any occurs, we will consult with the Data Safety Monitoring Board who will have authority to terminate the study, remove patients from participation, etc.

As stated in background section 1.1, suicidal ideation, suicide attempts, and non-suicidal self-injurious behaviors are common in this population. Therefore, these behaviors are not considered to be unexpected adverse events during the course of this study, unless they are directly attributable to study procedures.

## **5.2 Study Schedule**

1. Screening visits (3-6 hours, divided over multiple (usually 2-3) visits, usually remote) include the consent process, baseline clinical measures, and eligibility decision.
2. Neurofeedback session (~ 3 hours) includes arrival, final safety checks, mindfulness training, functional MRI scans and neurofeedback in MRI scanner, and debriefing procedures.
3. DBT skills group psychotherapy: ~120 minutes weekly for 20 weeks, ~ 30 minutes of surveys to complete ~ every 5 weeks.
4. Repeat MRI scans at DBT week 16, and 2 months after DBT ends are each ~ 90 minutes.
5. Repeat surveys for ~ 30-45 minutes at timepoints 1 and 2 months after DBT ends.
6. Some participants may be asked to participate in focus groups about the acceptability of the intervention.

## **5.3 Informed Consent**

Consent forms describing in detail the study intervention, study procedures, and risks are given to the participant and written documentation of informed consent is required prior to starting intervention/administering study intervention. The following consent materials are submitted with this protocol:

MIND-BPD Compound Authorization Form

